### Statistical analysis

The statistical analysis will be computed using SPSS Statistics software, version 27 (IBM, Chicago, IL, USA). The data analyses will be conducted by a statistician. Continuous variables will be summarized using standard measures of central tendency and dispersion, either as mean and standard error, or median and interquartile range. Dichotomous or categorical variables will be summarized by frequencies or denominators and percentage.

Kinesiophobia, lumbar endurance, and joint position sense will be compared between patients and controls using appropriate statistical tools. Kinesiophobia scores will be correlated with lumbar extensor endurance and proprioception joint position errors, pain intensity, and functional ability. Chi-square test will be used to find the association between kinesiophobia and lumbar endurance and joint position sense. Spearman rank correlation will be used to find the correlation between kinesiophobia, pain, and functional ability. Simple and multiple binary logistic regression will be used to determine crude and adjusted odds ratio for kinesiophobia, lumbar position sense and kinesiophobia, and lumbar endurance.

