**Material and methods:**

This case-control study will have 200 patients with CLBP and 400 controls. Kinesiophobia, lumbar endurance, and lumbar position sense will be assessed with Tampa Scale, Soren’s lumbar extensor test, and lumbar repositioning test respectively. Secondarily, the pain intensity will be assessed with visual analog scale and functional ability with Patient-specific Functional Scale in patients with CLBP. Lumbar endurance and joint position sense will be compared between subjects with and without kinesiophobia. Kinesiophobia scores will be compared with lumbar extensor endurance and proprioception joint position errors, pain intensity, and functional ability. Simple and multiple binary logistic regression will be used to determine crude and adjusted odd’s ratio for kinesiophobia, lumbar position sense and kinesiophobia, and lumbar endurance.

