#### Kinesiophobia

Fear of movement/injury or reinjury will be assessed using the Tampa Scale for Kinesiophobia (TSK), a scale with 17 self-reporting items with scores ranging from 17 (absence of fear) to 68 (highest fear) [46]. Tampa Scale for Kinesiophobia has been reported to have good reliability in patients with CLBP [47].

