#### Lumbar extensor endurance

All these experiments will be conducted in a laboratory setting. The subjects will be tested during a 1-h session and will be asked to undergo a body weight-dependent isometric back extension (Sorensen) test on a horizontal table [48]. Sorensen test will be performed in the prone position, with the iliac crests aligned with the table edge and the lower limbs fixed by straps at the ankles and below the knees. During the test, the participants will be instructed to keep their body (head, arms, and trunk) unsupported, horizontal to the ground, as long as they could, with their arms crossed at the chest [48]. To maintain the horizontal position throughout the test, the investigator will give them verbal feedback, and the test will be ended when they could not hold the test position. Verbalized encouragement will be provided throughout the test. The participants will be instructed to maintain the lumbar lordosis position as stable as possible. The endurance will be recorded by investigator with the help of a stopwatch in seconds. A chair with cushioned seat (or with a pillow over the seat) will be placed in front of the subject so that he can support himself if fatigued during the test. The stopwatch will be stopped as soon as the subject gets fatigued or can no longer sustain the position [48].

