For target lumbar positioning (TLP), the examiner guided in a slow steady pace that subject’s lumbar spine reached to a predetermined target, 50% of the maximum ROM. This range will be chosen so that all subjects could achieve it. The spine will be maintained in the target position for 5 s, subjects will be asked to remember the position, and the lumbar spine will be guided to a neutral position [49]. Subjects will then be asked to actively reposition by bending the spine to the target position. When the subjects reach the reference position, relocation accuracy will be measured in degrees [49]. Subjects will perform a total of three trials for each movement direction (flexion, lateral bending). The average of three trials will be used for analysis. The order in which movement directions will be tested will be randomized using a simple lottery method. Only the absolute error will be taken as a measurement; absolute error is the difference between the actual angles relative to the target angle and thus has no directional bias when compared to constant error or relative error.

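### Endurance in seconds, position error in degrees and a 17-68 TSK score are analysed by chi-square and, for the only covariate-adjusted model, binary logistic regression, which coarsens the data needlessly

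*Protocol article*

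**What the plan says.** All three measures are collected on fine scales.

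- Endurance, section Lumbar extensor endurance: "The endurance will be recorded by investigator with the help of a stopwatch in seconds".
- Position sense, section Lumbar repositioning tests: the error is in degrees, averaged over three trials, and "Only the absolute error will be taken as a measurement".
- Kinesiophobia, section Kinesiophobia: "a scale with 17 self-reporting items with scores ranging from 17 (absence of fear) to 68 (highest fear").

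The Statistical analysis section then names three analyses that link them.

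- A test of association: "Chi-square test will be used to find the association between kinesiophobia and lumbar endurance and joint position sense".
- A regression: "Simple and multiple binary logistic regression will be used to determine crude and adjusted odds ratio for kinesiophobia, lumbar position sense". The sentence goes on to pair kinesiophobia with endurance in the same way. This is the only model with covariates.
- A correlation of the TSK scores with endurance and position errors, with no covariates. Spearman's method is named only for pain and functional ability.

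The abstract also treats kinesiophobia as a yes/no attribute: "Lumbar endurance and joint position sense will be compared between subjects with and without kinesiophobia". The Sample size section plans on its prevalence (70% in cases, 10% in controls) and mentions subgroup analysis as a further way to handle confounding. The text shown gives no cut-off for any of the three measures.

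**The concern.** The relation of kinesiophobia to endurance and position sense is the core of the study's aims, and the Discussion presents the handling of confounders as what makes the findings novel and generalizable. The methods named for that relation do not fit the data. A chi-square test discards the ordering and spacing of seconds, degrees and score points. A binary logistic model of endurance or position error does the same to the outcome, so confounders are adjusted for on a coarsened scale.

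The cost is power and precision in the one adjusted analysis, and dependence of the odds ratio on where the cuts fall. An odds ratio for poor endurance is also harder to interpret than a difference in seconds per TSK point.

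**Working it through.** The article gives no power, effect size or information figure for this association, so there is no figure of its own to reproduce. The size of the loss can be derived under stated assumptions.

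**Inputs from the article.** 200 cases and 400 controls; kinesiophobia in 70% of cases and 10% of controls. Pooled share: (0.70 × 200 + 0.10 × 400) / 600 = 180 / 600 = 30%. A 70/30 and a 30/70 split have the same efficiency, so one figure serves for cases alone and for the pooled sample.

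**Assumptions.** Bivariate normal variables, the outcome cut at its median, two-sided 5% test, true correlation 0.20. None of these is in the article.

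**Step 1: information kept by cutting one variable.** Cutting a normal variable so that a share p lies on one side keeps φ(z_p)² / [p(1 − p)].

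- Median split: 0.3989² / 0.25 = 0.637, a loss of 36%.
- 70/30 split: 0.3477² / 0.21 = 0.576, a loss of 42%.

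**Step 2: both variables cut.** The efficiencies multiply.

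- Both at the median: 0.637 × 0.637 = 0.405, a loss of 59.5%; 200 patients carry the information of about 81.
- TSK at 70/30, outcome at the median: 0.576 × 0.637 = 0.366, a loss of 63%; 200 patients carry the information of about 73.
- Less even outcome cuts cost more: with TSK at 70/30 and the outcome at 20% or 10%, the loss is 72% or 80%.

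**Step 3: match these to the named methods.** A two-by-two chi-square cuts both variables, so Step 2 applies. Binary logistic regression forces only the dependent variable to be binary. With endurance or position error as that variable and TSK left as a score, the loss is the 36% of Step 1. With kinesiophobia entered as yes/no, it is the 60 to 63% of Step 2.

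**Step 4: power.** Approximate power is Φ(√n × 0.20 × √efficiency − 1.96).

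| Analysis | n | √n × 0.20 × √eff. | Power |
|---|---|---|---|
| Both continuous | 200 | 14.14 × 0.200 = 2.83 | 81% |
| Outcome cut at median | 200 | 14.14 × 0.160 = 2.26 | 62% |
| Both cut (70/30, median) | 200 | 14.14 × 0.121 = 1.71 | 40% |
| Both cut (30/70, median) | 600 | 24.49 × 0.121 = 2.97 | 84% |

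Simulation agrees: about 82% for continuous data, 60 to 64% for the outcome alone cut, and 40% for both cut at n = 200. A version with a covariate in the model gave 81%, 60% and 41%. The n = 600 line applies one correlation to the pooled sample; a mixture of cases and controls may not follow a single normal distribution, so that line is a guide only.

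**The case against.** **The adjusted model may lose less, or nothing.** A reader might infer that about 60% of the information is lost in the only adjusted analysis. The article does not support that as a fact. The regression sentence does not clearly name its dependent variable or say that TSK is dichotomised in the model. The third aim includes factors associated with CLBP itself, and where the outcome is case/control status logistic regression is the right model. This stands, and is why the loss is given as a range by reading. It does not remove the point: the same sentence pairs kinesiophobia with position sense and with endurance, and the PECO summary lists those two as outcomes.

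**The full scales are used elsewhere.** A reader might infer that the plan never analyses the scores as measured. It does, by correlation, so the crude association is covered. That analysis has no covariates and cannot replace an adjusted one.

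**Power may be ample.** A reader might infer that the study is underpowered. The article does not say whether these tests use the 200 cases or all 600 participants, and at 600 even the both-cut test has about 84% power at a correlation of 0.20. The loss is relative and avoidable; it does not show that the study must fail.

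**Cut-offs may exist.** A reader might infer that cuts will be picked to suit the result. Fig. 1, which specifies the outcomes, is not shown, and an analysis plan may fix them. The missing cut-offs are therefore not the finding. Cut-offs fixed elsewhere would not cure the choice of method. Chi-square also allows more than two categories, which would lose less than a two-way split.

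**Conclusion.** The concern holds in a limited form. The chi-square test categorises both sides of a relation measured on fine scales, and the only covariate-adjusted model named is one for a binary outcome. For endurance and position error, that means a loss of about 36% of the information if only the outcome is cut at its median, and about 60 to 63% if TSK is cut too. The second reading is the likelier one, given the comparison of subjects with and without kinesiophobia, but it is not certain for the logistic model.

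These sizes rest on normality, the splits shown and, for power, an assumed correlation of 0.20. The raw data are collected in full, so nothing is lost beyond repair. Severity: should be fixed, rather than must be fixed.

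**What to change.** In the Statistical analysis section:

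1. Make linear regression of hold time in seconds (log-transformed if skewed) and of mean absolute error in degrees on the continuous TSK score the main analysis, crude and adjusted for the confounders. Report the slope with its 95% confidence interval.
2. State the analysis set. For the secondary aim, fit the model within CLBP patients. If cases and controls are pooled, include case/control status and its interaction with TSK, so that the difference between the groups is not mistaken for a TSK slope.
3. Keep chi-square and logistic regression of dichotomised endurance or position error as supportive analyses, at cut-offs fixed before data are seen.
4. Keep logistic regression as the main model where the outcome is case/control status, and name the dependent variable of each model.

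The cost is analysis wording. The data and software are unchanged. The downside is that residuals and the need for transformation must be checked.

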## Abstract

**Background:**

Patients with chronic low back pain (CLBP) frequently present with kinesiophobia. Though large body of evidence reported the impact of kinesiophobia in patients with CLBP, there are paucity of studies in associating kinesiophobia to muscle endurance and position sense in patients with CLBP. The primary aim of the study is to compare the impact of kinesiophobia on lumbar extensor endurance, position sense in patient with CLBP, and asymptomatic individuals. Secondarily, we aim to examine the association between kinesiophobia and lumbar extensor endurance, position sense, pain intensity, and functional ability in patients with CLBP. Thirdly, we aim to assess the degree of association of various factors on CLBP, lumbar endurance, and position sense.

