**Discussion:**

The finding from this study can be generalized as this study has adequate sample size and subgroup analysis by adjusting the variables to draw a valid conclusion. The finding of this study will help the working physician to include assessment of kinesiophobia as part of musculoskeletal evaluation for patient with CLBP in a prospective diagnostic intervention.

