Kinesiophobia may produce a wide variety of physical and psychological effects that indirectly influence back pain to be maintained or recur or cause changes in the somatosensory system [26–28]. Studies in the past reported that patients with LBP had poorer ability to sense a change in lumbar position than control subjects [29–33]. Evidence reported that higher levels of pain-related fear are significantly associated with reduced amplitudes of movement and larger muscle activity and were consistent across subgroup and moderation analyses [27, 34]. Recent systematic reviews reported a moderate to strong evidence of associations between a greater degree of kinesiophobia, disability, and poorer quality of life in CMP. However, there was lack of consensus as there was heterogeneity present between all included studies in the systematic reviews in terms of population, outcome measures, pain conditions, and statistical parameters. Hence, an efficient comparison could not be made between their included studies. Moreover, none of the included studies specifically evaluated the possible mediating effect of kinesiophobia in CMP. Furthermore, confounding variables were not always explored in all included studies [18, 35]. Recent researches exploring the influence of kinesiophobia on CLBP and its various outcome are in the infant stage.

Chronic LBP is also associated with decreased endurance of the trunk extensor muscles [TE]. In addition, studies reported TE in chronic LBP participants to be significantly weaker than asymptomatic participants. The multi-factorial dysfunctions consistently reported in literature is the deconditioning of the lumbar extensor musculature, i.e., thoracic and lumbar erector spinae, multifidus, and quadratus lumborum [36, 37].

Long-term mechanical low back pain (LBP) results in inhibition and atrophy of the deep segmental muscles such as multifidus and overactivity of the longer superficial muscles of the trunk with resultant decreased dynamic activity and increased fatigability [38, 39]. Though the muscular endurance is reported to be affected in the patient with CLBP, no studies have explored the impact of kinesiophobia on lumber muscle endurance in patient with CLBP [40, 41] against asymptomatic subjects.

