### Sample size

As for the calculation of the sample size, the odds ratio taken is 2 with the prevalence of 70% kinesiophobia [17] among CLBP patients and assumed the prevalence of 10% kinesiophobia among the controls, with the minimum required sample size of 600 [200 cases + 400 controls]. The case-control ratio taken is 1:2. The controls will be invited participants/patients who have no complaints of lower back pain at the Thumbay Physical Therapy & Rehabilitation Hospital, Ajman. All possible confounding factors will be controlled through subgroup analysis in later part during data analysis. The patients and controls will be identified from the outpatient clinic prospectively.

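### For pain and functional ability, the protocol plans only an unadjusted Spearman correlation with kinesiophobia, and the unspecified subgroup analysis does not supply the missing adjustment

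*Protocol article*

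**What the plan says.** The secondary aim covers four outcomes in patients with chronic low back pain (CLBP): "Secondarily, we aim to examine the association between kinesiophobia and lumbar extensor endurance, position sense, pain intensity, and functional ability in patients with CLBP" (Abstract, Background).

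The Statistical analysis section assigns the methods. Two sentences mention pain and function, and both plan only a correlation:

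- "Kinesiophobia scores will be correlated with lumbar extensor endurance and proprioception joint position errors, pain intensity, and functional ability"
- "Spearman rank correlation will be used to find the correlation between kinesiophobia, pain, and functional ability"

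Adjustment appears in one sentence, which lists only the other two outcomes: "multiple binary logistic regression will be used to determine crude and adjusted odds ratio for kinesiophobia, lumbar position sense and kinesiophobia, and lumbar endurance".

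Outside that section there is a general promise under Sample size, "All possible confounding factors will be controlled through subgroup analysis in later part during data analysis", and the Abstract's Discussion paragraph says that "this study has adequate sample size and subgroup analysis by adjusting the variables to draw a valid conclusion".

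The Background criticises earlier work because "confounding variables were not always explored in all included studies". The main Discussion presents the handling of confounders as a reason why the findings will be novel and generalizable.

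**The concern.** The protocol adjusts two of the four secondary associations and leaves the other two crude, without giving a reason. Those two, pain intensity and disability, stand in the title as things that kinesiophobia influences.

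The PECO section links weight, inactivity, diet and smoking to low back pain disability, so the protocol itself treats these factors as related to at least one of the outcomes. It records them, along with age, gender, weight and height (Procedures), but no named analysis uses them for pain or function.

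If kinesiophobia also varies with these factors, the crude correlation mixes their contribution with that of kinesiophobia. The reader would then have no estimate that separates the two.

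**Working it through.** The point rests on which analyses are adjusted, and the article states no figure that needs reproducing. The arithmetic below asks whether subgroups could replace adjustment, whether adjustment is affordable, and how large the distortion might be.

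**1. Method by outcome (Statistical analysis section)**

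| Outcome | Crude analysis | Adjusted analysis |
|---|---|---|
| Lumbar endurance | correlation, chi-square, simple logistic | multiple logistic |
| Position sense | correlation, chi-square, simple logistic | multiple logistic |
| Pain (VAS) | Spearman | none named |
| Functional ability (PSFS) | Spearman | none named |

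**2. Could subgroups do the work?**

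- Patients: 200 cases (Sample size). The Discussion anticipates at least 80% for analysis, and 0.8 × 200 = 160.
- Categories (PECO section): smoking 4, alcohol 4, physical activity 4, diet 3.
- All four crossed: 4 × 4 × 4 × 3 = 192 cells, about one patient per cell.
- Without physical activity: 4 × 4 × 3 = 48 cells, so 200/48 = 4.2 or 160/48 = 3.3 patients per cell on average, before age, sex or weight.
- Taking subgroups one factor at a time avoids thin cells but leaves the other factors uncontrolled in each analysis.

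**3. Is adjustment affordable?**

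Age, sex and body mass index take one term each, smoking 3, alcohol 3 and diet 2, which makes 11. Physical activity would add 3, making 14. I used 15 as an upper bound. With k covariate terms, assuming two-sided 5% and 80% power, the smallest detectable correlation is approximately tanh[(1.960 + 0.842)/√(n − 3 − k)].

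| n | k = 0 | k = 15 |
|---|---|---|
| 200 | 0.197 | 0.205 |
| 160 | 0.220 | 0.231 |

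The loss is about 0.01 on the correlation scale.

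**4. How far could a crude correlation mislead? (illustration)**

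The document gives no covariate correlations, so every input here is assumed.

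*No true effect.* Take three independent covariates, each correlated a with both kinesiophobia and the outcome, all acting in the same direction. The crude correlation is r = 3a². The chance of a significant result in that direction is Φ(atanh(r)·√(n − 3) − 1.96).

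| a | r | n = 200 | n = 160 |
|---|---|---|---|
| 0.15 | 0.068 | 0.16 | 0.13 |
| 0.20 | 0.120 | 0.39 | 0.33 |
| 0.25 | 0.188 | 0.76 | 0.66 |

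The nominal two-sided rate is 5%.

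*A real association.* Suppose the crude correlation is 0.30 and one confounder correlates c with both variables. The partial correlation is (0.30 − c²)/(1 − c²):

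| c | 0.1 | 0.2 | 0.3 | 0.4 | 0.5 |
|---|---|---|---|---|---|
| Partial r | 0.29 | 0.27 | 0.23 | 0.17 | 0.07 |

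Weak confounding changes little, while strong confounding changes the conclusion.

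**The case against.** **The protocol does address confounding in general terms.** The Sample size section promises control of all possible confounders by subgroup analysis, without limiting it to certain outcomes, and the PECO section sets confounders beside kinesiophobia with pain and function among the outcomes. A reader might infer from the Spearman sentence that confounding is simply ignored. The document does not support that. What remains is that the promise names no strata, is not tied to these correlations and cannot adjust jointly at this sample size.

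**Half of the secondary aim is adjusted.** A reader might also infer that the whole aim repeats the weakness criticised in the Background. It does not: endurance and position sense go into the multiple logistic regression, although that sentence does not say whether it is run within patients. The Background also says only that confounders were not always explored, and lists this after heterogeneity and the absence of mediation analysis.

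**The aim is to examine association.** Spearman is a legitimate description of association for VAS and PSFS scores, and a fuller analysis plan may hold more. Both points have force. Even so, the article names a method for each pairing, adjusts some and not others, and claims more than description in its title and Discussion.

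**Adjusting for everything recorded could do harm.** In the mechanism set out in the Background, fear leads to avoidance of physical activity, and disuse goes with more pain. Physical activity may therefore lie on the pathway, and adjusting for it could remove part of the association of interest. This objection stands in full and shapes the fix.

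**Conclusion.** The point holds for pain and functional ability only. For these two outcomes the article names an unadjusted correlation and no adjusted analysis, and the general subgroup promise does not fill the gap. That is inconsistent with its handling of endurance and position sense and with its stated emphasis on confounding.

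The size of any bias cannot be established from the document. The 16% to 76% range at 200 cases (about 13% to 66% at 160) depends wholly on assumed correlations, on all confounders acting in one direction and on a true effect of exactly zero. That last assumption sits badly with the associations reported in the Background. A reader might take the range as this study's false-positive rate, and it is not that. The case for change rests on the missing adjusted estimate and the low cost of adding it. It concerns secondary outcomes and does not affect the primary comparison.

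**What to change.** 1. Keep the Spearman correlations of the Tampa Scale (TSK) score with VAS and PSFS, labelled as crude.
2. In patients with CLBP, add for each outcome either a partial Spearman correlation or a regression on the continuous TSK score. Adjust for age, sex, body mass index (from the recorded weight and height), smoking, alcohol and diet. Report the adjusted estimate with its 95% interval beside the crude figure.
3. Add physical activity in a sensitivity analysis only, and say why: the Background places it between fear and pain.
4. Describe the result as an association.
5. In the Sample size section, either name the subgroups or state that confounding is handled by the adjusted models.

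The cost is a change of wording and two more models on data already planned for collection. Precision falls negligibly: the detectable correlation moves from 0.197 to at most 0.205 with 200 patients, and from 0.220 to at most 0.231 with 160. The adjusted association may turn out smaller than the crude one, and the authors should be ready to report that.
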